# Seasonal variation in food security, lifestyle, nutritional status and its associated factors of the urban poor adolescents in Kuala Lumpur, Malaysia: research protocol of a prospective cohort study

**DOI:** 10.1186/s40795-023-00680-6

**Published:** 2023-02-02

**Keywords:** Food security, Urban poor adolescents, Healthy lifestyle, Climate change, Monsoon season

## Abstract

**Background:**

Climate change, obesity and undernutrition have now become a worldwide syndemic that threatens most people’s health and natural systems in the twenty-first century. Adolescent malnutrition appears to be a matter of concern in Malaysia, and this is particularly relevant among the urban poor population. Mounting evidence points to the fact that underlying factors of malnutrition are subject to climate variability and profoundly affect nutritional outcomes. Hence, it is interesting to examine seasonal variation in nutritional status and its associated factors of urban poor adolescents in Malaysia.

**Methods:**

This is a prospective cohort study following urban poor adolescents aged 10–17 years living in low-cost high-rise flats in Kuala Lumpur, Malaysia, across two monsoon seasons. The baseline assessment will be conducted during the onset of the Northeast Monsoon and followed up during Southwest Monsoon. Climate data will be collected by obtaining the climatological data (rainfall, temperature, and relative humidity) from Malaysia Meteorological Department. Geospatial data for food accessibility and availability, and also built (recreational facilities) environments, will be analyzed using the QGIS 3.4 Madeira software. Information on socio-demographic data, food security, lifestyle (diet and physical activity), and neighbourhood environment (food and built environment) will be collected using a self-administrative questionnaire. Anthropometric measurements, including weight, height, and waist circumference, will be conducted following WHO standardized protocol. WHO Anthro Plus was used to determine the height-for-age (HAZ) and BMI-for-age (BAZ). Anaemic status through biochemical analyses will be taken using HemoCue 201+® haemoglobinometer.

**Discussion:**

The study will provide insights into the seasonal effects in nutritional status and its associated factors of urban poor adolescents. These findings can be useful for relevant stakeholders, including policymakers and the government sector, in seizing context-specific strategies and policy opportunities that are seasonally sensitive, effective, and sustainable in addressing multiple challenges to combat all forms of malnutrition, especially among urban poor communities.

**Trial registration:**

The protocol for this review has not been registered.

## Background

Although many actions and efforts had been made, malnutrition in all forms, including overnutrition (overweight and obese) and undernutrition (underweight, wasting, stunting and micronutrients deficiencies), as well as diet-related non-communicable diseases (diabetes, cardiovascular diseases), continues to be alarming public health issues all over the world including both developed and developing countries [1]. According to Country Nutrition Report by Global Nutrition Report, Malaysia has been recently classified as one of the Asian countries that is currently experiencing a triple burden of malnutrition, where overweight coexists with stunting and anaemia [2]. This urges the need for urgent action to identify and address the root causes of public health issues.

As defined by World Health Organization (WHO)_,_ defines adolescents are young people aged between 10 and 19 years [3]. It is well recognized that adolescence is the vital period in the life span that experiences major anatomical, physiological, and social changes as a form of transition. During this transition from childhood to adulthood period, children begin to explore and develop their identities as a result of complex interactions with their families, communities, and culture that accompany all domains of autonomy development [4]. This dynamic period of human growth makes adolescents nutritionally vulnerable as the pubertal transition during this period is accompanied by a growth spurt where extra macronutrients and micronutrients are required [5, 6]. The burden of malnutrition can harm adolescents in multiple ways, including impaired growth, osteopenia, anaemia, retard sexual maturation, and these consequences have been shown to be associated with the early onset of chronic diseases in adulthood [7].

In this twenty-first century, climate change, obesity, and undernourishment have now become a worldwide syndemic that threatens most people’s health and natural systems globally in every part of the world [8]. While climate change requires decades or centuries to represent true shifts in the long-term means, what individuals experience in their everyday lives are simply anomalies around a stable mean, known as climatic variability [9]. Climate change is already showing significant implications for the food system and the food environment, subsequently affecting critical dimensions of food security. Thus, possess a risk to human health. People’s daily experiences with climatic variability, on the other hand, are contributing to alarming levels of malnutrition [10]. A systematic review of the existing efforts to quantify the effect of climate change on undernutrition confirmed the evidence of a significant but varied link between weather variables such as rainfall, extreme weather events, seasonality and temperature, and malnutrition at the household level [11–13]. Cumulative changes in the state of climate no matter in the short term or long term, can have profound effects on crop yields, fisheries, and livestock production. These changes in the food production system may result in economic losses and disturb the internal equilibrium food supply, resulting in food price spikes that obstruct food accessibility and affordability. Consequently, dietary patterns and food utilization have changed to adapt to these unfavourable situations. Besides, food utilization is also affected by factors such as food safety and nutritional quality aspects. These changes will hinder progress toward the eradication of malnutrition in all its forms [14, 15].

In Malaysia, the Global Food Security Index has dropped from the 28th in 2019 to 43rd in 2020, where resilience and natural resources, such as weather extreme, exposure to high-temperature rises, have been highlighted as one of the key dimensions leading to national food security deteriorates slightly [16]. Besides, urban poor communities tend to have greater exposure to natural hazards, direct dependence on climate-sensitive resources, and limited resources and capacity to adapt and cope with unexpected or immediate dangerous events [12]. Meanwhile, A study by UNICEF Malaysia [17] which focuses on urban poverty and deprivation in low-cost flats in Kuala Lumpur, reported that more than 1 in 10 children have less than three meals a day and experience undernourishment which is worse than the national prevalence [18]. The commodity inflation pressure due to reduced agricultural production might prompt a shift in their dietary patterns towards affordable yet unhealthy food supply. This raises questions about the implication of climate variability as an unprecedented confluence of pressure on food security and its associated threats to nutritional status among urban poor in Malaysia. A household study in Tanzania provides evidence that the increase in variability of temperature is associated with a decrease of about 11% in daily calorie intake [10]. A positive correlation is visible for maize and wheat prices with an increased average temperature in some countries, such as Bangladesh, Ethiopia, and Yemen [19]. Climate variability-related consequences such as a limited supply of vegetables during rainy days make vegetables more expensive and affect the overall consumption of healthful foods for this vulnerable population [12]. Hence, the occurrence of food insecurity appeared to be is one of the biggest problems among this population, and this forced the community to have a monotonous diet with poor nutrition, which over time can constrain children and adolescent’s growth and development [10, 20]. Without action, the likely increased risk of food insecurity and malnutrition brought on by climate change and variability are shouldered by most disadvantaged urban poor children and adolescents [20]. In addition, climate change, food security, and malnutrition are now commonly regarded as high-priority objectives for many countries in terms of sustainable development, as recognized by the UN Sustainable Development Goals (SDGs) [21].

Climate-related effects on malnutrition could also be reflected in food utilization and associated with the nutritional quality of food, its production and consumption, and food safety. A recent systematic review and meta-analysis by Stelmach-mardas et al. [22] that assessed the effect of season on food intake and total energy intake confirmed that season is a potential determinant of the intake of fruits, vegetables, eggs, meat, cereals, and alcoholic beverages and that an increase in energy intake was observed during winter or post-harvest season. In tropical countries such as Cambodia, the consumption of rice, starchy roots, vegetables and products, condiments, and spices tend to be higher during wet seasons, while more alcoholic and non-alcoholic beverages were consumed more during the dry seasons [23]. Another study conducted in the North of Ghana examined the effects of seasonal variation on dietary diversity was notable, especially in the consumption of vitamin A-rich fruit and vegetables where dark green leafy vegetables were consumed more during rainy seasons while deep yellow, orange, and red vegetables were consumed more during dry seasons [24]. Increased inter-seasonal climate variability thus intensifies nutrient intake fluctuations, exacerbating negative effects on nutrition. This is supported by the prevalence of seasonal variations in childhood malnutrition. A longitudinal study conducted in east rural Ethiopia found that higher prevalence of acutely malnourished children in the dry season compared to rainy seasons [25]. Contrarary On the other hand, the Ghana study reported better height-for-age and body mass index-for-age during the dry season compared to the wet season [26].

Another possible link between climate variability and malnutrition, specifically obesity, is the reduction of physical activity. Past research reported that when the weather is too cold or too hot to go outdoors, even just for a walk or a jog can simply reduce physical activity levels [27]. Previous systematic review and meta-analysis studies suggested that children’s engagement in physical activity varies by season, whereby healthier physical activity level was observed in Spring compared with other seasons [28]. A study in the US reported that adolescents were less physically active during winter and on rainy and short sunlight days, while higher physical activity during warmer and rain-free days [29]. This further confirmed that climate variability does significantly influence the level of physical activity.

To address key issues of malnutrition, environmental exposure in relation to food and physical activity should also be considered as a part of key determinants. A neighbourhood environment that promotes unhealthy dietary intake and a sedentary lifestyle can lead to an increase in malnutrition [30]. In the increasingly urbanized world, cities dwellers are facing challenges of having limited or difficult access to healthy food markets, known as ‘food deserts’ or confronted with an abundance of unhealthy food that is high in calories, low in nutrients, and processed foods, known as ‘food swamp’. These phenomena are particularly more common among urban communities that face a high degree of poverty [31]. The lack of availability and access to nutrient-dense food may have serious adverse consequences on the nutrition and well-being of children and adolescents [31, 32].

Similarly, built environments, including the combinations of coexisting stimuli such as recreational facilities, green spaces, parks, land use, and transport infrastructures, influence an individual’s ability to achieve the recommended level of physical activity. Urbanization had to cause the reduction of physical activeness due to the urban environmental quality and the setting [33], whereby high-density traffic, limited sidewalks, parks, and recreational facilities as well as overcrowding and safety in the neighbourhood such as crime and violence are commonly reported as the significant barriers that could discourage, or crease active living and causing changes in lifestyle behaviour [34, 35]. Other important environmental variables include mixed land use, transportation system, and the density of built spaces which are related to the walkability of a neighbourhood, consequently, weight status [36].

As Malaysia is located close to the equatorial line, hence no extreme weather changes can be observed and are free from inter-seasonal variability as seen in four-season countries [10]. However, the climate system of Malaysia is largely influenced by the Southeast Asia Maritime Continent monsoon, which consists of two monsoon regimes, Southwest Monsoon (summer monsoon, late May to September) and Northeast Monsoon (winter monsoon, November to March) [37, 38]. With this, it is hypothesized that seasonal variation in food security, dietary consumption, and physical activity behaviours that leads to nutritional changes, as observed in the four-season countries, may also be observed in Malaysia during the two monsoon seasons. Nevertheless, these anticipated changes and their long-term effects were rarely studied in Malaysia. Additionally, most of the research on seasonality are generally focuses on young children [24, 25, 39, 40] and adults [22, 23], and adolescents are often understudied despite their apparent vulnerability is observed. With this, It is unclear of the possible long-term impact of climate variability on the changes in nutrition-related components in Malaysia. This makes the need to study the effects of seasonal variability on malnutrition and its associated factors especially among the urban poor adolescent population in Malaysia.

## Methods

### Study aim

The main aim of the study is to examine the seasonal variation in food security, lifestyle factors, neighbourhood environmental factors, and nutritional status of the urban poor adolescents in Kuala Lumpur, Malaysia. To achieve the aim, the specific research objectives to be investigated in the study are as follows:To determine the food security, lifestyle factors, neighbourhood environmental factors, and nutritional status of the urban poor adolescents in Kuala Lumpur, Malaysia.To determine the seasonal differences in food security, lifestyle factors, and nutritional status among urban poor adolescents in Kuala Lumpur, Malaysia.To determine the effects of season on food security, lifestyle factors, neighbourhood environment, and its effects on the nutritional status of the urban poor adolescents in Kuala Lumpur, Malaysia.

### Study design

This is a cohort study that stemmed from two cross-sectional studies that will be carried out during the onset of the Northeast Monsoon season and will be followed up during the Southwest Monsoon season to capture a different season. Recruitment of the subjects will begin upon obtaining ethical clearance from the Institutional Ethics Committee of UCSI University [Reference code.: IEC-2021-FAS-03)] and permission to conduct the study from Kuala Lumpur City Town Hall (DBKL) [Reference code: DBKL/JPKKB/SPZ/29–3 Jld 13 (48)].

### Study setting and sampling method

This study followed a multistage stratified random sampling design **(**Fig. 1**)**. First, a complete list of the People’s Housing Programme (*Perumahan Awam, PA or Program Perumahan Rakyat, PPR*) (*n* = 53), located in Kuala Lumpur is obtained from the Kuala Lumpur City Town Hall (*Dewan Bandaraya Kuala Lumpur, DBKL*) and further stratified into four zone areas based on the zone office management by DBKL. Subsequently, three flats from each zone area will be randomly selected (*n* = 12). A convenience sampling method will be applied for the recruitment of the subjects whereby the residential president of PA/PPR shared e-flyers through social media platforms with the residents for the recruitment of the adolescents via the parents. In addition, adolescents will be also approached by door-to-door recruitment methods at all the residential blocks. All adolescents from all ethnicities within the selected flats are invited to participate in the study. The purpose and procedures of the study will be explained to the adolescents and their parents/guardians. A detailed information sheet will be provided for a better understanding of the study. Parents/guardians will be requested to sign a written informed consent to allow their child’s participation, and assent will be obtained from adolescents to indicate their willingness to participate before the commencement of the study. Data collection will be conducted by enumerators who have been trained, monitored, and supervised throughout the study. Each adolescents will be given a unique identification number to ensure anonymity. The flow diagram of the study is depicted in Fig. 2.

**Fig. 1 Fig1:**
[figure not shown]
Multistage stratified random sampling method of the study

**Fig. 2 Fig2:**
[figure not shown]
Data collection procedure

### Inclusion and exclusion criteria

There are a few inclusions and exclusion criteria set for the adolescents to be recruited and qualified to participate in this study. The criteria are as below:

#### Inclusion criteria

Malaysian adolescents aged between 10 to 17 years old.Adolescents currently living in low-cost high-rise flats in Kuala Lumpur at least for the past 12 months.Healthy adolescents with no physical and learning disabilities, as confirmed by parents.

#### Exclusion criteria

Adolescents who are under any special diet or diet restriction.Adolescents who have chronic medical problems such as heart disease, diabetes, cancer, etc.Adolescent females who are pregnant or lactating.Adolescents who were infected with COVID-19 at the point of the study.

### Sample size calculation

The sample size will be calculated for the baseline cross-sectional analysis of this study. The sample size is determined using single proportion formula [41] for estimating prevalence. Based on the proportion of adolescents who were obese in Kuala Lumpur, Malaysia (15.8%) [14], with the desired level of confidence at 95% and desired level of precision of 0.05, a minimum of 204 subjects are required for the study. In consideration of the non-response rate and attrition rate among adolescents, the sample size is increased (+ 25%) to 256 adolescents.

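### The 0.05 precision behind the minimum of 204 assumes a simple random sample; the design is 12 randomly selected flats with convenience recruitment inside them

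*Protocol article*

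**What the plan says.** Under Sample size calculation, the protocol article states its scope: "The sample size will be calculated for the baseline cross-sectional analysis of this study". On method it says "The sample size is determined using single proportion formula". The inputs are an obesity proportion of 15.8% and 95% confidence, and the result is "desired level of precision of 0.05, a minimum of 204 subjects are required for the study". For non-response and attrition, "the sample size is increased (+ 25%) to 256 adolescents". The section mentions no design effect, intra-flat correlation or expected loss rate.

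Under Study setting and sampling method, the article opens with "This study followed a multistage stratified random sampling design", and the caption of Fig. 1 uses the same label. The 53 housing schemes are stratified into four zones and three flats per zone are drawn at random, 12 in all. For people within those flats the method changes: "A convenience sampling method will be applied for the recruitment of the subjects". Residents are reached by e-flyers shared through the residents' president and by door-to-door visits in all blocks, and every adolescent in the selected flats is invited.

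Objective 1, under Study aim, is to describe food security, lifestyle, neighbourhood and nutritional status in Kuala Lumpur's urban poor adolescents. The limitations in the Discussion deal with generalising to all Malaysian adolescents and with COVID-19. They do not mention self-selection within flats.

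**The concern.** The single-proportion formula gives its stated precision only when individuals are drawn independently and at random. Neither condition is provided here.

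- **Clustering.** Adolescents in the same flats share an environment and may resemble each other. No limit of one adolescent per household is stated, so siblings may enter together.
- **Selection.** Within flats, those who take part are those who respond or are reached and agree. This is a possible bias, and no sample size formula allows for it.

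The precision of 0.05 is the only planning property the article states. If it stands beside a random-sampling label, the Objective 1 prevalences may be read as probability-sample estimates for Kuala Lumpur's urban poor adolescents, with sampling error of plus or minus 5 points. The design as described supports neither part of that reading.

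**Working it through.** **Inputs from the protocol article.** p = 0.158; 95% confidence (z = 1.96); half-width d = 0.05; minimum 204; target 256; 12 flats out of 53.

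**Input not in the article.** The ICC within flats. I assume 0.01 to 0.05.

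**Step 1: reproduce the stated figures.**

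n = z² p(1 − p) / d² = 1.96² × 0.158 × 0.842 / 0.05² = 204.4

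204.4 × 1.25 = 255.5, which rounds to 256.

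Both figures reproduce. Because 204 equals the formula without any multiplier, no design effect has been included.

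**Step 2: half-width as a simple random sample.**

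h = 1.96 × √(p(1 − p)/n)

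- n = 204: 0.0501
- n = 256: 0.0447

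The minimum of 204 has no slack. The 256 has slack equal to a design effect of 256/204.4 = 1.25.

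**Step 3: half-width with 12 flats.** Assume equal flat sizes, m = n/12, and no allowance for stratification or for the finite number of flats.

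DEFF = 1 + (m − 1) × ICC, and h is multiplied by √DEFF.

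| Assumed ICC | n = 204 (m = 17): DEFF | Half-width, points | n = 256 (m = 21.3): DEFF | Half-width, points |
|---|---|---|---|---|
| 0.01 | 1.16 | 5.4 | 1.20 | 4.9 |
| 0.02 | 1.32 | 5.8 | 1.41 | 5.3 |
| 0.05 | 1.80 | 6.7 | 2.02 | 6.3 |

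At n = 204, DEFF exceeds 1 for every positive ICC, so the half-width always exceeds 5 points.

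**Step 4: largest ICC at which 256 still meets 0.05.**

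ICC = (256/204.4 − 1) / (21.33 − 1) = 0.252 / 20.33 = 0.0124

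**Step 5: effect of the finite number of flats.** Twelve of 53 flats are drawn, a fraction of 0.226. An approximate correction applied to the between-flat part gives DEFF = 1 + (m × 0.774 − 1) × ICC. The limit for 256 then rises to 0.252 / (21.33 × 0.774 − 1) = 0.252 / 15.5 = 0.016. At n = 204 the bracket is 17 × 0.774 − 1 = 12.2, so any positive ICC still takes the half-width above 5 points.

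**Step 6: what the widths leave out.** All these figures are sampling error under random selection within flats. With convenience recruitment they carry no allowance for the difference between participants and non-participants.

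**The case against.** The case on the other side has real force in several places.

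- **The calculation is arithmetically sound.** 204 and 256 both reproduce. This stands: the defect is an unmet assumption.
- **The shortfall depends on an ICC the article does not give.** With all 256 analysed, 0.05 is met for sampling error at an ICC of 0.01, and allowing for 12 of 53 flats moves the limit from about 0.012 to about 0.016. Zone stratification may help a little more. This stands, so it is too strong to say that the precision will be missed.
- **Convenience recruitment is disclosed next to the label.** All blocks are visited and all adolescents in the selected flats are invited, and the flat stage is random. This lessens the risk of misleading a careful reader. It does not make the label right for the stage at which people are selected, and the limitations do not pick the point up.

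A reader might also infer faults that the document does not support:

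- **A 25% loss that is not covered.** The article states a 25% increase and no loss rate. Multiplying by 1.25 is what a 20% loss would call for (204/0.80 = 255). Loss at follow-up also does not shrink the baseline sample, which is what the calculation is for.
- **Wider intervals for other prevalences.** The article claims 0.05 for obesity only.
- **No figure for the seasonal change.** The calculation is openly limited to the baseline analysis, so this is an omission and not a wrong statement.

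**Conclusion.** The point holds as a mismatch between the stated precision and the stated design. The article condenses a fuller protocol, but this is more than missing detail: the minimum it prints is exactly the simple-random-sample figure, and the sampling it describes is not a simple random sample.

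For a prevalence of 15.8%, the expected half-width is 5.4 to 6.7 points with 204 analysed and 4.9 to 6.3 points with 256. This rests on an assumed ICC of 0.01 to 0.05, 12 flats of equal size, and no gain from stratification or the finite number of flats. Self-selection within flats comes on top and cannot be quantified from the document.

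The weight is moderate. No test, outcome or decision rule depends on the 5-point figure, and the observed data will yield their own intervals. What needs correcting is the planning claim and the label under which the Objective 1 prevalences will be read.

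**What to change.** Make three changes of wording:

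1. **Sample size calculation.** State that 0.05 is nominal, for obesity under simple random sampling. Add the expected half-width for 12 flats under a stated ICC range, for example 4.9 to 6.3 points with 256 analysed and an ICC of 0.01 to 0.05.
2. **Study setting and sampling method, and the Fig. 1 caption.** Describe the design as stratified random selection of flats with convenience recruitment of residents.
3. **Limitations in the Discussion.** Add self-selection within flats as a limit on the Objective 1 prevalences.

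No further enrolment is asked for; the status section reports recruitment and baseline collection complete on 30 April 2022. The cost is a few sentences and a slightly less favourable stated precision.
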